## 8.2 Participants

Eligibility criteria:

- Age ≥8 (day of their 8th birthday or older) to 17 years (one day before their 18th birthday). This age-group has been selected to ensure participants have had complete (2 year) exposure to the PITC intervention
- Written informed consent from the guardian
- Assent from the child

If there is more than one child in the household in the eligible age-range then all the children in the household will be tested. Inclusion of all children in the eligible age-group will provide an estimate of prevalence of HIV among siblings and allow exploration of “clustering” of HIV among children in households.

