## 3.3 Study Design

The study will be conducted in the main PHCs of six suburbs in Southwest Harare. Each participating PHC will offer PITC routinely to 6-15 years olds over a two year period, a well as decentralised HIV care including ART initiation. Thus, children who test HIV-positive through PITC will be offered HIV care at the same PHC. At the end of two years of implementation of PITC, an anonymised HIV prevalence survey of 8-17 years olds from randomly selected dwellings in the suburbs served by the study PHCs will be conducted. The prevalence of *undiagnosed* HIV infection in the community following two years of PITC will provide an indication of the effectiveness of primary-care based routine HIV testing in providing high enough coverage of HIV diagnosis in this age-group (>80% of children diagnosed). The survey will also provide data on overall HIV prevalence by age in the considered age-group.

Children who test HIV-positive through PITC at the PHCs and reside in the study suburb where the clinic is located will be recruited into a trial of a VLW-delivered intervention to support to households of HIV-infected children aged 6-15 years. Stratified sampling will be used with randomisation of participants within clinics (1:1) to either a) primary care based HIV care or b) primary care-based HIV care plus treatment support provided by VLWs.

The intervention will be delivered over an eighteen month period, with formative work carried out to inform the design of the intervention. This will consist of qualitative interviews with care-givers of HIV-positive children attending for HIV care and health care providers (nurses, doctors, counsellors and pharmacists) at Harare Central Hospital as well as Community-based Organizations to understand the needs of households with HIV-infected children.

Children testing HIV positive at the PHCs including those recruited into the trial, will be recruited into a clinical cohort study. Data from routine clinic visit (including height, weight, clinical symptoms, incident clinical events and adherence) will be collected. In addition, detailed growth monitoring, lung function testing and a psychosocial assessment (i.e. schooling, guardianship, and disclosure) will be carried out at pre-defined intervals. The HIV care cohort will also provide a platform for immunological studies of slow-progression of HIV infection.

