## 4.5 Participant selection, inclusion and exclusion criteria

The inclusion criteria for participation in the trial will be:

- age between 6 years (day of their 6th birthday and older) and 15 years (a day before their 16th birthday)
- test HIV-positive following PITC in the PHC
- willing to have their HIV care at the PHC
- usual residence in the study suburb where the PHC is located
- informed consent by parent and assent from child to participate

The exclusion criteria for participation in the trial will be:

- age <6 years or ≥16 years
- usual residence outside the study suburb where the PHC is located
- previously tested HIV+ positive and receiving care (clinical or psychosocial)
- not planning to access HIV care at the PHC

All participants enrolled into the trial will automatically be offered enrolment into the cohort study. Additionally, any children aged 6-15 years who test HIV-positive following PITC after enrolment for the trial is completed, will also be approached for recruitment into the clinical cohort study.

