# METHODS AND PROCEDURES

## 5.1 Routine PHC based PITC

All children aged 6-15 years attending for acute care at primary health care clinics (PHC) in seven of the 10 high density suburbs of southwest Harare (Highfield, Glen View, Budiriro, Kuwadzana, Mufakose, Dzivarasekwa, Glen Norah) will be offered routine provider-initiated testing and counselling (PITC) during a two year period. Training on HIV testing and counselling of children will be provided through PSI.

A research assistant will be based at the clinic and will identify children eligible for PITC and refer them for HIV testing to PHC counsellors/nurses. After clinic registration, the standard approach to PITC developed by the Ministry of Health and Child Welfare will be used. All eligible clinic attendees will be given brief standard pre-test counselling followed by an offer of HIV testing and post-test counselling. Guardian consent will be required for children to undergo HIV testing. Children attending without a guardian will be given information about HIV testing and encouraged to re-attend with a guardian for HIV testing.

HIV test results will be given to the child and their guardian at the same clinic visit, with age-appropriate explanation of HIV test results given to the child. Children who test positive will be offered enrolment into HIV care at the PHC where they test. Biological parents, guardians and natural siblings of children who test HIV-positive will be offered HIV testing. Attendees who decline HIV testing will be assessed for their presenting health problem by the clinic nurse. PITC outcome will be recorded as accepted/ absent guardian/ testing for subject declined /testing for guardian declined.

HIV testing kits will be provided by the National HIV Program. The research assistants will ensure that a supply of testing kits is always available at the PHCs. Diagnostic HIV testing will be carried out using two HIV rapid tests (Abbott Determine™ and SD Bioline™) run in parallel. Discordant specimens will be resolved using a third rapid HIV test (INSTI™).

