### 11.2.2 Post-PITC Prevalence Survey Sample Size Estimates

We propose to survey children aged 8-17 years from approximately all households in 90 randomly selected CEAs to investigate the prevalence of undiagnosed HIV infection. Assuming an HIV prevalence of 3% among older children and a refusal rate of 25%, a sample size of 6,500 for the cross-sectional prevalence survey will include approximately 118 HIV infected individuals. We anticipate that the prevalence of undiagnosed HIV to drop by >50% as a result of optimal PITC implementation at PHCs. This should provide a 95% CI of around 40%-60% around a prevalence of undiagnosed HIV of 50% (i.e. precision of 10%),

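### The 8-17 survey band does not give complete two-year PITC exposure (16-17-year-olds had only part of it), and the expected 118 infected children does not follow from the section's own inputs

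*Protocol*

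**What the plan says.** Protocol 3.3 sets the intervention: "Each participating PHC will offer PITC routinely to 6-15 years olds over a two year period". Section 5.1 uses the same range. The upper limit is spelled out in 4.5, for the trial, as "age between 6 years (day of their 6th birthday and older) and 15 years (a day before their 16th birthday". Section 9.2.1 records attendees up to 16 but determines the PITC counts among ages 6-15.

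The survey follows: "At the end of two years of implementation of PITC, an anonymised HIV prevalence survey of 8-17 years olds" (3.3). Its eligibility rule is "Age ≥8 (day of their 8th birthday or older) to 17 years (one day before their 18th birthday" (8.2), and the reason given is "This age-group has been selected to ensure participants have had complete (2 year) exposure to the PITC intervention". Section 3.3 says the survey will indicate whether clinic-based testing achieves "high enough coverage of HIV diagnosis in this age-group (>80% of children diagnosed").

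On size, section 11.2.2 assumes 3% prevalence and 25% refusal and states that "a sample size of 6,500 for the cross-sectional prevalence survey will include approximately 118 HIV infected individuals". It gives a 95% interval of about 40% to 60% around 50% undiagnosed. The survey box in Figure 1.1 gives 6,000 children instead of 6,500.

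**The concern.** The survey band is the PITC band moved up by two years. That ensures every surveyed child was age-eligible on the day PITC began. It does not ensure eligibility throughout, because a child who was 14 or 15 at the start passed the 16th birthday during the two years.

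This matters for interpretation. Section 11.1 rules out a survey before PITC, so the post-PITC survey is the only measurement of the undiagnosed share in the community. The first hypothesis in 3.1 assumes almost all infected children will consult at least once during a two-year window. If children without that window are pooled with those who had it, infections left undiagnosed after they ceased to be eligible count against the programme.

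The infected count is a separate and smaller matter. It underlies the only precision statement for the survey, and it cannot be obtained from the inputs stated beside it.

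**Working it through.** **Exposure by age at survey.** Inputs: PITC from the 6th birthday to the day before the 16th (3.3, 4.5, 5.1), lasting two years; survey ages 8 to under 18 (8.2), taken at the end of the two years (3.3). A child aged *a* at survey was *a* − 2 at the start and stayed eligible until 16, so eligible time = min(2, 16 − (*a* − 2)) = min(2, 18 − *a*) years.

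| Age at survey | Age at start | Eligible time | Mean if ages are uniform |
|---|---|---|---|
| 8-15 | 6-13 | 2 years | 2.0 |
| 16 | 14 | 1 to 2 years | 1.5 |
| 17 | 15 | under 1 year (1 year at exactly 17.0) | 0.5 |

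Two of ten single-year groups, 20% of the range, fall short. Mean eligible time over 8-17 is (8 × 2 + 1.5 + 0.5)/10 = 1.8 years.

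**Illustrative effect on the undiagnosed share.** Assumptions: 80% undiagnosed at the start (11.1); a constant rate of decline *r* while eligible; no diagnosis after the 16th birthday; infections spread evenly over the ten ages. If U is the share left after two full years, *r* = ln(0.80/U)/2. The mean over eligible times *s* to *t* is 0.80 × (e^(−*rs*) − e^(−*rt*))/*r*. Three values of U: 20% (the >80% criterion), 40% (half of 80%; 11.2.2 anticipates a drop of more than half) and 50% (the value at which 11.2.2 gives precision).

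| U at full exposure | *r* | Age 16 | Age 17 | Pooled 8-17 | Shift |
|---|---|---|---|---|---|
| 20% | 0.693 | 28.9% | 57.7% | 24.7% | 4.7 points |
| 40% | 0.347 | 47.8% | 67.6% | 43.5% | 3.5 points |
| 50% | 0.235 | 56.4% | 71.3% | 52.8% | 2.8 points |

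First row: (8 × 20 + 28.9 + 57.7)/10 = 24.7. With 146 infected, the half-width at 24.7% is 1.96 × √(0.247 × 0.753/146) = 7.0 points, giving 17.7% to 31.7%, which includes 20%.

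**Expected infected count.** The figure of 118 is not reproduced:

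- 6,500 × 0.75 × 0.03 = 146, if 6,500 is the number approached.
- 6,500 × 0.03 = 195, if 6,500 is net of refusal.
- With the 6,000 in Figure 1.1: 6,000 × 0.75 × 0.03 = 135, or 6,000 × 0.03 = 180.
- Changing one input at a time, 118 needs 118/(0.75 × 0.03) = 5,244 approached, or a prevalence of 118/(6,500 × 0.75) = 2.42%, or participation of 118/(6,500 × 0.03) = 60.5%, that is 39% refusal.

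**Precision.** Half-width = 1.96 × √(p(1 − p)/m) under simple random sampling. The largest design effect that still gives ±10 points is 0.01 × m/(1.96² × p(1 − p)). The stated ±10 at 50% needs m = 96.

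| Infected m | Share p | Half-width | Largest design effect for ±10 |
|---|---|---|---|
| 118 | 50% | 9.0 points | 1.23 |
| 146 | 50% | 8.1 points | 1.52 |
| 117 (146 × 0.8, ages 8-15) | 50% | 9.1 points | 1.22 |
| 117 | 20% | 7.2 points | 1.90 |

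**The case against.** The band has a coherent logic: ages 8-17 after two years are the closed cohort that was eligible when PITC began. A child aged 14 or 15 at the start was a target of the programme, and one missed before turning 16 is a genuine miss. The band is also used consistently across the survey text. Age is recorded for each child (8.3) and prevalence by age is planned (3.3), so an age breakdown is possible without new data. All this stands. It supports keeping 16-17-year-olds in the survey and reporting the overall figure, but it does not make the sentence in 8.2 true.

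A reader might infer that pooling could turn a successful programme into an apparent failure. The documents do not support that. Section 3.3 treats the survey as indicative and sets no test or pass/fail rule, and the 4.7-point shift in the most demanding scenario lies within sampling error. The scenarios also assume no diagnosis after 16. Section 4.3 describes client-initiated and facility testing for people over 16, while noting that facility testing in practice follows symptoms or request. Access is therefore limited but not nil, which makes this assumption an upper bound.

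A reader might also infer that 118 is simply a slip for 146. The protocol does not show which input is out of date. For instance, 6,500 × 1.8% = 117, but that borrows the trial's prevalence from 11.2.1 and ignores refusal. The error is also conservative: 118, 135, 146, 180 and 195 all exceed the 96 needed for ±10 under simple random sampling.

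**Conclusion.** The rationale in 8.2 is wrong for ages 16 and 17, about a fifth of the age range. They were partly exposed, averaging about one year of eligibility, not unexposed. The direction of the effect, a higher undiagnosed share, follows whenever less eligible time means less diagnosis. The size, roughly 3 to 5 points, is illustrative and rests on an 80% starting value, a constant decline, evenly spread infections and no diagnosis after 16.

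The count of 118 does not follow from its stated inputs and needs reconciling. It is 146 only if 6,500 is the number approached and the other inputs in 11.2.2 stand. The discrepancy does not by itself threaten the stated precision. Clustering might: section 8.1 samples 90 census enumeration areas and takes all eligible households and children in them, and 8.2 expects clustering within households. Section 11.2.2 mentions no allowance for this.

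**What to change.** 1. In 8.2, state that the 8-17 band is the cohort age-eligible when PITC began, that ages 8-15 had the full two years, and that 16-17-year-olds had part of it.
2. Judge the >80% diagnosed criterion on ages 8 to the day before the 16th birthday. Report 16-17 separately as partly exposed, and give the overall 8-17 figure alongside.
3. Reconcile 6,000 (Figure 1.1) with 6,500 (11.2.2), say whether that number is before or after refusal, and restate the expected infected count. If the 11.2.2 inputs stand and 6,500 is the number approached, this is 146, of whom about 117 are aged 8-15 if infections are evenly spread by age.
4. Give precision at 20% undiagnosed, the value that the >80% criterion turns on, as well as at 50%, with a stated design effect for enumeration areas and households.

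Fieldwork is unchanged. The cost is about 20% fewer infected children in the main estimate and less room for clustering: with 117 infected, ±10 points at 50% holds only up to a design effect of about 1.2, against about 1.5 with 146. At 20% undiagnosed the limit with 117 is about 1.9.

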## 8.3 Collection of data and biological samples

The selected households will be visited and anonymised HIV testing will carried out on all children resident in the households, with guardian consent and participant assent.

An oral mucosal transudate (OMT) test will be collected from all participants to test for HIV antibodies. Participants will also be asked to provide a urine sample or dried blood spot (DBS) sample to test for antiretroviral drug concentration. This will identify those individuals who may under-report their HIV status.

Each household will be allocated an anonymous identification number and one form will be completed per household with provision for more than one child per household with separate HIV testing numbers identification numbers which are linked to the household per child. A questionnaire will be administered for each household whereby information on the following will be collected:-

- Demographics information on the household:
- The numbers and ages of all children of the household
- Socioeconomic variables, including difficulties in providing food, or in finding money to go to clinic if anyone in the household gets sick
- Demographic information on each child who participates:
- Age
- Sex
- Orphanhood status
- Grade in school (or not attending school and reason)
- Absenteeism from school due to illness
- History of HIV testing (including date of, place of and reason for test) and whether accessing HIV care/on ART

Risk factors for HIV infection at household level will be identified. If consent is declined or there is no guardian available in an eligible household to provide consent to participate, demographic information about the household will be requested from a key informant. This information will be used to define likely HIV status of children through imputation.

Undiagnosed and untreated HIV infection will be defined through self-reported past HIV-testing episodes, and self-reported chronic care medication (specifically, any ART, cotrimoxazole and IPT) being received at the time of interview. Clinical patient held records and any documentation of previous HIV test will be used to confirm the information given.

Guardians will be encouraged to bring children who have not tested before or cannot provide proof of testing to the PHCs for diagnostic testing and written information about HIV testing will be provided. Routine HIV testing for children and adolescents will be provided at the PHC of the suburb where the prevalence survey will be taking place supported by a ZENITH study research assistant and nurse. In addition, participants who test positive will automatically be offered HIV care and treatment at the same clinic. A CD4 count test will be done to ensure prompt assessment.

All participants of the prevalence survey will be offered free HIV testing (as described above). Each household will be randomised to receive 1) nothing, 2) a USD 2.00 incentive or 3) entry into a prize draw where they stand to get USD5.00, USD10.00 (this will be a draw so participants may get nothing) if the children in the selected households participate in the prevalence survey and come to the clinic for HIV counselling and testing. A flyer with benefits of HIV testing and the strategy the household has been randomised to will be given to participants. The clinic will carry out HIV testing according to National Guidelines with consent from the guardian (of participants aged <16 years) and assent from the participant (obtained verbally when they attend the clinic for HIV testing).

The standard operating procedures and forms used for the survey are listed in Appendix 18.2.

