## 3.4 Study outcomes

### 3.4.1 PITC intervention

- Proportion of attendees who 1) accept HIV testing and 2) test HIV+ve following PITC
- Prevalence of undiagnosed HIV infection in the community two years post PITC implementation

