### 9.2.3 Post-PITC HIV Prevalence Survey

Participants’ guardians will be asked if they know their child(ren)’s HIV status and whether their child(ren) is/are on cotrimoxazole or ART. Data on whether a selected participant has accepted or refused anonymous HIV testing will be collected, as well as number of visits required before a guardian is identified. The following will be determined:

- Cumulative total of all participants found to be HIV-positive on anonymous HIV testing, who were known to be HIV-positive prior to the survey
- Cumulative total of all participants found to be HIV-positive on anonymous HIV testing, who were previously undiagnosed
- Cumulative total of all participants who were known to be HIV positive and are not currently on currently on cotrimoxazole or ART

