## 12.2 Diagnostic and anonymised HIV testing

For the HIV prevalence survey, participants will be asked to provide an oral mucosal test (OMT) sample for anonymised testing. The samples will be read on the same day. Each of the specimen containers will only bear the study ID of the participants. Diagnostic HIV testing in PHCs will be carried out according to National guidelines. Two rapid tests (Abbott Determine™ and SD Bioline™) will be run in parallel with a 3rd rapid test (INSTI™) with used as a tiebreaker in case of discordant results between the first two tests.

Urine or DBS samples will be collected from participants to check for presence of ART. Urine samples of participants with HIV-positive OMT results will be individually tested for presence of ART. Urine samples of participants with HIV-negative result will be pooled (20 samples pooled) with individual testing of each sample should one pooled batch test ART-positive. DBS samples will be tested individually for ART.

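### The survey's definition of undiagnosed and untreated HIV infection omits the ART assay collected to detect under-reporting, so the undiagnosed share is biased upward

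*Protocol*

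**What the plan says.** The survey supplies one of the two PITC outcomes in Protocol section 3.4.1: "Prevalence of undiagnosed HIV infection in the community two years post PITC implementation". Section 3.3 sets the benchmark for adequate coverage at more than 80% of infected children diagnosed, which means fewer than 20% undiagnosed.

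Section 8.3 does two things that do not meet:

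- It adds a drug assay: "Participants will also be asked to provide a urine sample or dried blood spot (DBS) sample to test for antiretroviral drug concentration". The reason follows: "This will identify those individuals who may under-report their HIV status".
- It then states the operative rule: "Undiagnosed and untreated HIV infection will be defined through self-reported past HIV-testing episodes, and self-reported chronic care medication", the medication being ART, cotrimoxazole or IPT. The one check named is: "Clinical patient held records and any documentation of previous HIV test will be used to confirm the information given".

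Section 9.2.3 describes the data behind the counts: "Participants’ guardians will be asked if they know their child(ren)’s HIV status and whether their child(ren) is/are on cotrimoxazole or ART". One of the counts is: "Cumulative total of all participants found to be HIV-positive on anonymous HIV testing, who were previously undiagnosed". The assay is not mentioned there.

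Section 12.2 says how the assay is run. For OMT-positive children: "Urine samples of participants with HIV-positive OMT results will be individually tested for presence of ART". Urine from OMT-negative children is pooled in batches of 20, with individual testing if a pool is positive; DBS samples are tested individually. It does not say what a positive result does to a child's classification.

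**The concern.** The assay exists because families may not report a diagnosis. A rule built on their report, checked against papers the same families choose to show, will tend to fail for exactly those children. The protocol's own Table 2.1 lists stigma and delayed disclosure among the problems of this population, so non-disclosure is a realistic risk.

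Each such child on ART is counted as undiagnosed when the study holds a laboratory result showing treatment. The same sentence defines untreated infection, so a child with drug detected can also be recorded as untreated. The error has one direction: it makes PITC coverage look worse than it is.

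There is a second gap. Section 12.2 looks for ART in OMT-negative children, but the diagnosed and undiagnosed counts in 9.2.3 both require a positive anonymous HIV test. A child found this way has no stated place in the results.

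**Working it through.** **1. Reading the sections together.** Take an OMT-positive child whose family reports no positive test and none of the listed medications, shows no record, and whose sample contains ART.

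- 8.3, definition: undiagnosed and untreated.
- 8.3, purpose of the assay: an under-reporter, hence already diagnosed.
- 9.2.3: takes status and treatment from the guardian and gives no rule for the assay.
- 12.2: produces the assay result and gives no rule for its use.

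The only stated classification rule gives the first answer.

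**2. The plan's own precision figure.** Section 11.2.2 expects about 118 infected children and a 95% CI of around 40%-60% at 50% undiagnosed. Half-width = 1.96 × √(0.5 × 0.5 / 118) = 0.090, giving 41.0%-59.0%. This agrees with the stated interval. The 118 does not follow from the stated inputs: 6,500 × 0.75 × 0.03 = 146 (half-width 0.081). That is a separate matter; the shares below do not depend on which number is used.

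**3. Bias from leaving the assay out.** Let

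- U = true undiagnosed share. 20% is the section 3.3 benchmark; 50% is the planning value in 11.2.2.
- a = share of diagnosed children on ART. Assumed 70%, borrowed from the trial's ART-start assumption in 11.2.1; none is given for the survey population.
- d = share of those treated children whose families neither disclose nor show a record. Assumed 10-30%; the documents give no figure.

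Recorded undiagnosed share = U + (1 − U) × a × d, so the avoidable bias is (1 − U) × a × d.

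| U | d | Avoidable bias | Recorded share |
| --- | --- | --- | --- |
| 20% | 10% | 0.8 × 0.7 × 0.1 = 5.6 points | 25.6% |
| 20% | 30% | 0.8 × 0.7 × 0.3 = 16.8 points | 36.8% |
| 50% | 10% | 0.5 × 0.7 × 0.1 = 3.5 points | 53.5% |
| 50% | 30% | 0.5 × 0.7 × 0.3 = 10.5 points | 60.5% |

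At U = 20% this is about 7 to 20 of 118 children. The bias equals the planned 10-point precision when a × d = 0.10 / 0.80 = 0.125 at U = 20%, or 0.10 / 0.50 = 0.20 at U = 50%. With a = 70%, that is d of about 18% and 29%.

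**4. What the assay cannot remove.** If the same 10-30% also applies to the 30% of diagnosed children not on ART, a further 0.8 × 0.3 × (0.1 to 0.3) = 2.4-7.2 points remains at U = 20%. With the assay in the rule the share would read 22.4%-27.2%.

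**The case against.** The strongest reply is that this is a gap in wording, not a decision to discard the assay. The section states why the sample is taken, and individual testing of OMT-positive children makes sense only if the result is used. The rule combining self-report, records and assay may sit in the survey SOPs (Appendix 18.2) or an analysis plan, neither of which is shown. This stands as far as intent goes: a reader might infer that the sponsor chose to exclude the assay, and the documents do not support that. It does not remove the point, because the protocol is not silent. It states a definition, and that definition omits the assay. An SOP that used it would depart from the protocol's text.

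Three further limits stand.

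- Section 9.2.3 might be read as restricting its counts to self-report. It does not say so; its wording is compatible with using the assay. It only fails to bring the assay in.
- The definition is broader than a single question. A family must withhold the test history and every listed medication, and show no record. The non-disclosure rate here is therefore the rate after records have been checked, and it may be low.
- It is tempting to class every child with ART detected as infected and diagnosed, whatever the oral fluid test shows. About 4,729 of 4,875 participants (6,500 × 0.75, less 146) would be OMT-negative. At an assumed assay specificity of 99.5% (none is given), about 24 false positives would enter as diagnosed, and a true 20% (29/146) would read about 17% (29/170). That flatters PITC.

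**Conclusion.** The point holds for OMT-positive children. The stated definition ignores a result the study will hold, and the undiagnosed share is biased upward against the benchmark of more than 80% diagnosed. The direction follows from the text. The size does not: 5.6-16.8 points rests on an assumed true 20% undiagnosed, 70% of diagnosed children on ART, and 10-30% of those neither disclosing nor showing a record. It applies to children who give a sample and have detectable drug.

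A reader might attribute all non-disclosure to this omission, which on the same inputs would be 8-24 points (a recorded 28%-44%). That is not supported: 2.4-7.2 of those points come from diagnosed children not on ART, whom no drug assay can find.

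The point concerns the survey outcome only and does not touch the randomised comparison. The definition should be amended before the survey is analysed.

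**What to change.** Amend sections 8.3 and 9.2.3 as follows.

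- An OMT-positive child with ART detected is classed as previously diagnosed and treated, regardless of self-report.
- Undiagnosed means OMT-positive, with no reported or documented positive test or HIV care, and no ART detected in a sample actually tested.
- OMT-positive children without an assay result are classified by self-report and records, and their number is reported separately. A missing sample is not treated as no drug detected.
- OMT-negative children with ART detected are shown on a separate line and counted as infected and diagnosed only in a sensitivity analysis.
- The self-report-and-records figure, without the assay, is given as a sensitivity analysis.
- State as a limitation that the assay cannot find diagnosed children who are not on ART and do not disclose.

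If the survey SOPs already contain a combining rule, align the protocol text with it and cite it. Samples and assays are already planned, so the cost is redrafting two sections and adding a few lines to the results tables.
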